**Methods:**

We will use a retrospective cohort study design with the population-based Surveillance, Epidemiology, and End-Results database linked to the Medicare Health Outcomes Survey (SEER-MHOS). Older women (≥65 years) who were diagnosed with low-risk breast cancer in 1998-2014, received breast-conserving surgery, and participated in MHOS 1998-2016 are eligible for this analysis. The latent class analysis clustering method will be used to identify each patient’s prediagnosis comorbidity burden, and HRQOL will be evaluated using the Short Form 36/Veterans RAND 12-Item Health Survey scales. The inverse-weighted estimates of the probability of treatment will be included to control for treatment selection bias and confounding effects in subsequent analysis. The association of RT with HRQOL trajectory will be evaluated using inverse-weighted multilevel growth mixture models. The inverse-weighted Cox regression model will be used to obtain hazard ratios with 95% CIs for the association of RT with survival outcomes. Differential effects of RT on both outcomes according to comorbidity burden class will also be evaluated.

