#### Statistical Analysis Plan

Regarding the descriptive analyses, the baseline characteristics of the study population will be described in terms of the mean and SD for continuous variables and frequencies with percentages for categorical variables. Descriptive analyses will be conducted to compare demographic, tumor-related, and treatment-related factors for the study population by their treatment status (BCS and RT vs BCS only). Differences in continuous variables and categorical variables will be assessed by *t* tests and chi-square tests, respectively. All analyses will be conducted using SAS 9.4 (SAS Institute Inc.) and R 4.0.1 (R Core Team), and a 2-tailed α level of .05 will denote statistical significance.

The probability of the treatment received by a particular person will be estimated by generalized boosted models using receipt of RT as the dependent variable and the baseline characteristics, such as age at diagnosis, race/ethnicity, smoking status, income, education, SEER region, rurality, disease stage, tumor grade, tumor subtype, and year of diagnosis, as the independent variables. Then, the inverse of the probability of receiving the treatment the patient actually received conditional on the observed covariates will be calculated and included as a weight for each patient in subsequent analyses [41]. Balances in potential confounding factors between the treatment groups will be assessed using diagnostic tools, including chi-square tests for categorical variables, *t* tests for continuous variables, and the standardized mean differences between 2 groups [42]. The standardized mean difference will be calculated as the difference in means or proportions divided by a pooled estimate of SD. A standardized mean difference≥10% will be considered as evidence of imbalance [43].

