We will also test for the existence of a differential effect of RT on the HRQOL trajectory according to the comorbidity burden class by incorporating interaction terms in the model. If we lack the power to detect statistically significant differences according to comorbidity level but point estimates for the effect of RT indicate that meaningful differences are present across levels of comorbidity, separate estimates will be reported for each comorbidity class. As each participant completed MHOS at different time points, growth mixture modeling is more flexible and sensitive than traditional repeated-measures analysis [44]. It can also capture nonlinear patterns [44].

Regarding the sensitivity/subgroup analysis, if the sample size allows, subgroup analysis by age and tumor stage will be conducted to examine whether the findings are generalizable to all patients satisfying the eligibility criteria.

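### RT effects are to be evaluated by comorbidity class, but weighted balance is checked only between the two overall RT groups and class is not a named propensity input, so class-specific confounding could go unseen, most of all in Aim 2

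*Protocol article*

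**What the plan says.** The abstract's Methods state the objective for both outcomes: "Differential effects of RT on both outcomes according to comorbidity burden class will also be evaluated". The two aims in the Introduction each include the interaction with comorbidity burden and hypothesise which class will show the largest effect. The Aim 1 Statistical Analysis Plan tests the interaction. If power is lacking but point estimates differ meaningfully, it adds that "separate estimates will be reported for each comorbidity class".

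The weights come from a generalized boosted model whose named inputs are "age at diagnosis, race/ethnicity, smoking status, income, education, SEER region, rurality, disease stage, tumor grade, tumor subtype, and year of diagnosis". The list is introduced as examples. Comorbidity class is not in it, nor in the list of potential confounders under Aim 1, Measurements, where class is the effect modifier.

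On balance the plan says: "Balances in potential confounding factors between the treatment groups will be assessed using diagnostic tools, including chi-square tests for categorical variables", then t tests for continuous variables "and the standardized mean differences between 2 groups". The cut-off follows: "A standardized mean difference≥10% will be considered as evidence of imbalance". No check within class is named. The Aim 2 Statistical Analysis Plan obtains its weights by the same procedures.

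On adjustment beyond the weights, the Aim 1 level-2 regression on RT and class is adjusted for confounders. Aim 2 describes a weighted Cox model and states no further covariate adjustment.

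**The concern.** A class-specific RT effect compares RT with no RT among women of one class, so what matters is balance inside that class. The stated diagnostic does not examine that comparison. If, say, older age steers women away from RT in one class but not in another, the opposing imbalances can cancel in the whole cohort. The overall table then looks clean while each class estimate is confounded, in different directions. The apparent effect modification, which both aims set out to find, could then be a difference in age or stage mix between the RT groups within classes.

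A lesser matter is that chi-square and t tests stand beside the SMD as balance tools, and at these sample sizes they seldom react to an imbalance at the plan's own 10% limit.

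**Working it through.** The article gives no balance calculation to reproduce, so the check has four steps.

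**Inputs from the article.** N = 465 (Aim 1) and 634 (Aim 2); 3-5 classes anticipated; RT use above 50%; SMD limit 0.10; two-sided α .05. **Assumed:** the cohort's RT share, class sizes, covariate relations and prognostic strengths, none of which the article gives.

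**1. What chance alone does within a class.** If RT were randomised within class, SE(SMD) = √(1/n₁ + 1/n₀) and P(|SMD| > 0.10) = 2[1 − Φ(0.10/SE)]. Assume 69% RT and classes of 40/30/20/10%. For the largest class at N = 465, n = 186, so SE = √(1/128.3 + 1/57.7) = 0.159 and P = 53%.

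| N | 40% | 30% | 20% | 10% |
|---|---|---|---|---|
| 465 | 53% | 58% | 66% | 75% |
| 634 | 46% | 52% | 60% | 71% |

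So about half to three-quarters of covariates would pass 10% in a class with no confounding at all. A raw count of within-class exceedances says nothing about bias.

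**2. Separating chance from systematic imbalance.** The simulation had three classes of equal expected size, about 65% RT, 10 covariates, and logistic weights standing in for the boosted model. One covariate was tracked. Its log-odds slope on RT was either zero in every class or ran from −0.3 to +0.3 across classes. Entries are the median of the largest within-class weighted SMD. The median overall SMD was at most 0.016 throughout.

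| N | Slope by class | Class not in model | Class as main effect | Class-by-covariate terms |
|---|---|---|---|---|
| 465 | none | 0.170 | 0.171 | 0.034 |
| 465 | differs | 0.341 | 0.380 | 0.045 |
| 634 | none | 0.126 | 0.132 | 0.030 |
| 634 | differs | 0.352 | 0.353 | 0.037 |
| 20,000 | none | 0.027 | 0.021 | 0.003 |
| 20,000 | differs | 0.309 | 0.314 | 0.006 |

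With no class difference in slope, the imbalance fades as N grows, so it is chance. With a class difference it stays near 0.31 at 20,000, so it is systematic. Adding class as a main effect does not remove it; class-by-covariate terms do.

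**3. What a systematic imbalance does to a class effect.** For a continuous outcome the unadjusted bias in SD units is about r × SMD, where r is the covariate's correlation with outcome. With r = 0.5 (assumed), 0.5 × 0.31 = 0.16 SD, or 1.6 points on a summary score with SD 10. A simulation of this kind with logistic weights gave bias up to about 0.25 SD under its settings. Class-by-covariate weights or within-class covariate adjustment removed nearly all of it without raising the root mean squared error.

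For mortality, as illustration only, assume an age SD of 6 years and 9% higher hazard per year. An age SMD of 0.2 is 0.2 × 6 = 1.2 years, and 1.09^1.2 = 1.11. An SMD of 0.31 is 1.86 years, and 1.09^1.86 = 1.17.

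**4. Significance tests against the 10% rule.** The smallest SMD significant at .05 is 1.96√(1/n₁ + 1/n₀). Over RT shares of 50-80% it is 0.18-0.23 at N = 465 and 0.16-0.20 at N = 634. Power at SMD 0.10 is 14-19% and 17-24%.

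**The case against.** The strongest reply has four parts.

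- *Within-class imbalance is mostly noise.* Step 1 grants this. A reader might infer that, because most within-class SMDs would exceed 10%, the class-specific effects are confounded. That does not follow: a randomised study with classes of this size would look the same, and class-specific intervals largely reflect that variation.
- *The hazard-ratio shift is small beside the uncertainty.* This stands. A 10% class in Aim 2 has about 63 women, 44 with RT and 20 without at 69% RT. Even if all died, the 95% limits would be a factor of exp(1.96√(1/43.7 + 1/19.7)) = 1.7 either way, and 2.9 at an assumed 25% mortality. But bias is not carried by the interval, and the larger classes have narrower ones.
- *The plan already contains much of the remedy.* Boosted models can fit interactions without their being specified, and Aim 1 adjusts level 2 for confounders. Both points stand in part. Boosting can find class-specific structure only if class is an input. The example-style input list and the Introduction's promise to include all potential confounders leave room for class but do not name it. For Aim 2, Measurements says the confounders match Aim 1, and the proportional-hazards check mentions covariates, but an adjusted Cox model is not spelled out.
- *A condensed article may leave subgroup balance tables to a fuller plan, and the SMD is already the only diagnostic with a balance threshold.* It is fair that the tests supplement the SMD and nothing lets them override it, so that part is minor. But the article does fix the contrast, the tools and the cut-off, and the contrast it fixes is not the one that the class-specific effects need. Separate Aim 1 class estimates are conditional; the interaction model uses within-class contrasts in any case.

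**Conclusion.** The concern holds in a limited form. The stated balance check covers the overall RT comparison, while both aims also draw conclusions by comorbidity class, and class is not a named propensity input. If covariate-RT relations differ by class, overall SMDs can look clean while class-specific effects are biased: in the illustration, a within-class SMD near 0.31, or about 0.16 SD of outcome at r = 0.5, and up to about 0.25 SD under other settings. Aim 2 is the more exposed; Aim 1 is partly protected by its level-2 adjustment.

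This shows a risk that the plan would not detect. It does not show that this cohort's class effects are biased, and the documents cannot support that stronger reading. The sizes rest on assumed RT share, class sizes, slopes and prognostic strengths, and on logistic rather than boosted weights. The 11% hazard-ratio shift is an illustration only.

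**What to change.** In the Aim 1 Statistical Analysis Plan, carried to Aim 2:

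1. Name comorbidity class as an input to the boosted propensity model, with enough tree depth to fit class-by-covariate interactions.
2. Report weighted SMDs within each class as well as overall, for both aims, beside class size and the SMD expected by chance. Do not make 10% an automatic trigger within class, since it would fire for about half to three-quarters of covariates by chance.
3. For class-specific RT estimates, adjust the outcome model, notably the Aim 2 Cox model, for a short prespecified set of strong prognostic confounders such as age and stage.
4. Use the weighted SMD, not chi-square or t tests, as the balance criterion. This is minor good practice.

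The cost is one extra table per aim, some refitting, and somewhat more variable weights in the smallest class. The article's Results section says the classes had been characterised before further analysis, so all of this can be specified in advance.

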## Methods

### Overview

This observational study uses a retrospective cohort design, and the study population comprises older women with low-risk breast cancer who received BCS as a primary treatment and took part in the Medicare Health Outcomes Survey (MHOS). As depicted in Figure 1, the women are first clustered according to their prediagnosis comorbidity burden. Next, we will obtain the propensity score-based probability of receiving adjuvant RT based on observed potential confounding variables. Then, inverse probability weights will be calculated and adjusted for in subsequent analyses. We will examine the effect of RT on 2 outcomes: differences in the patterns of HRQOL trajectories over 10 years post diagnosis and 5-year survival outcomes.

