#### Measurements

The primary exposure variable will be adjuvant RT. We will consider BCS alone and BCS with adjuvant RT as the treatments. The SEER data provide information on radiation treatment and the sequence of surgery and radiation.

The outcomes of Aim 1 will be HRQOL scores measured over a 5-10 years of follow-up (ie, prediagnosis through post-treatment). MHOS measures HRQOL using the Medical Outcomes Study 36-item Short Form (SF-36) through the year 2005 and the Veterans RAND 12-item Health Survey (VR-12) from the year 2006 onwards. These 2 questionnaires have been validated in many languages and are widely used in HRQOL research, including that involving breast cancer patients [38]. The NCI developed algorithms to convert SF-36 scales to VR-12 scales; hence, the latter will be used across all cohorts in the current study. The VR-12 items correspond to 8 health domains, namely physical functioning, role limitations due to physical problems, role limitations due to emotional problems, bodily pain, social functioning, mental health, vitality, and perceptions of general health. These 12 items are then summarized into 2 summary scores: the physical component summary score and the mental component summary score. These 2 summary scores are standardized scores (mean 50, SD 10), which are normed based on the general US population. A total of 465 women who met the eligibility criteria for Aim 1 completed MHOS multiple times (an average of 3 times). We will sort the data according to the prediagnosis (T_0_) and postdiagnosis (T_1_…T_10_) timelines, specifying the time lapse from the cancer diagnosis. The prediagnosis HRQOL (T_0_, n=465) will be assessed using the survey conducted within 24 months prior to the diagnosis date recorded in SEER. The postdiagnosis HRQOL (T_1_…T_10_) will be assessed using the survey completed after the diagnosis of breast cancer. We collected 465 data points for the precancer diagnosis, 508 data points within 2 years postdiagnosis, 166 data points for 2-<5 years postdiagnosis, and 92 data points for ≥5 years postdiagnosis. The number of patients who completed MHOS in each time frame is presented in Table 1.

**Table 1 table1:** Number of patients who completed MHOS in each time frame (N=465).

Survey time to cancer diagnosis (months), t	Prediagnosis and postdiagnosis HRQOL timelines	n (%)
–24<t<0	T_0_	465 (100)
0≤*t*<12	T_1_	253 (54)
12≤*t*<24	T_2_	255 (55)
24≤*t*<36	T_3_	79 (17)
36≤*t*<48	T_4_	50 (11)
48≤*t*<60	T_5_	37 (8)

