Regarding the estimation of RT and comorbidity effects on HRQOL trajectory, we will use a multilevel growth mixture model with surveys clustered within the women to test whether a difference exists in the patterns of HRQOL trajectories with receipt of RT and comorbidity class after controlling for confounders. At level 1, we will first regress woman i’s HRQOL change, which describes how each woman’s HRQOL depends on time t. This procedure will provide the intercept and slope of the time predictor for each woman. At level 2, we will regress each woman’s intercept and slope on her RT treatment (yes/no) and comorbidity class, adjusted for confounders. This procedure will feature how individual HRQOL change trajectories vary across treatment groups (RT) and comorbidity burden classes (COM). Equation (1) presents a simplified model with no covariates, predicting HRQOL from years after diagnosis (TIME), radiation treatment (RT), and comorbidity class (COM). It will estimate the intercepts and slopes for the group of women.

HRQOL_ti_ = γ_00_ + γ_01_RT_it_ + γ_02_COM_i_ + γ_10_TIME_it_ + γ_11_RT_i_TIME_it_ + γ_12_COM_i_TIME_it_ + error **(1)**

where

γ_00_=Estimated average HRQOL in the year of diagnosis for women who did not receive RT

γ_01_=Value added to the average HRQOL if the women received RT

γ_02_=Value added to the average HRQOL due to the comorbidity class

γ_10_=Change in HRQOL for all women for each year from diagnosis

γ_11_=Additional change for each year if the women received RT

γ_12_=Additional change for each year due to the comorbidity class

A significant negative value on γ_11_ will indicate that women who receive RT experience steeper declines in HRQOL over time than those who did not receive RT, while a significant negative value on γ_12_ will indicate stronger HRQOL declines due to the comorbidity burden.

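### Aim 1, Equation (1): with no term separating before from after diagnosis, the rule on γ11 cannot tell a one-time drop with RT from a steeper yearly decline, and γ01 mixes prior group differences with an RT effect

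*Protocol article*

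**What the plan says.** Protocol article, Aim 1, Measurements: the outcomes are "HRQOL scores measured over a 5-10 years of follow-up (ie, prediagnosis through post-treatment". The first of them, T0, "will be assessed using the survey conducted within 24 months prior to the diagnosis date recorded in SEER". T0 is therefore part of the outcome series and precedes any RT.

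Aim 1, Statistical Analysis Plan: at level 2, both the intercept and the slope depend on RT as a yes/no variable. Equation (1) has one linear TIME term and no before/after term or knot. It defines γ00 as "Estimated average HRQOL in the year of diagnosis for women who did not receive RT", γ01 as the amount that RT adds to the mean, and γ11 as the extra yearly change with RT. A significant negative γ11 "will indicate that women who receive RT experience steeper declines in HRQOL over time than those who did not receive RT".

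The RT main effect carries the subscript it, while RT in the interaction carries only i. The text after the equation says that growth mixture modelling can follow curved paths, but specifies no curved term. The Overview sets the target as "differences in the patterns of HRQOL trajectories over 10 years post diagnosis and 5-year survival outcomes".

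**The concern.** γ01 applies to T0 as fully as to T1-T10. Any health difference between the groups before diagnosis therefore enters a coefficient that the plan describes as what RT adds.

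A change that occurs once, around treatment, has no term of its own. A straight line through the low and high sides of a step tilts, and the plan reads that tilt as continuing decline. A woman could then be told that RT makes quality of life fall faster every year when the truth is a single or temporary loss. The Discussion says the results are meant to support shared decisions about RT, so the distinction matters.

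**Working it through.** **Inputs from the document.** Table 1 counts for T0 to T10: 465, 253, 255, 79, 50, 37, 29, 21, 17, 8, 17.

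**The plan's own figures reproduce.** 253+255 = 508; 79+50+37 = 166; 29+21+17+8+17 = 92. The total is 465+508+166+92 = 1,231, or 1,231/465 = 2.65 surveys per woman, which rounds to the stated average of 3. At 5 years or more: 92/1,231 = 7.5%, with 17 points in the last bin.

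**Assumptions.** Times are bin midpoints: -1 for T0, then 0.5, 1.5, …, 8.5, and 9.5 for the open-ended T10. The effect sizes are illustrative. The RT share (60%) and the variance components are not in the document.

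**Step 1: what Equation (1) returns.** Let d(t) be the true RT minus no-RT difference and w the Table 1 counts. An unweighted linear fit gives

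γ11 = [Σwtd - (Σwt)(Σwd)/N] / [Σwt² - (Σwt)²/N]

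γ01 = Σwd/N - γ11·Σwt/N

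Here N = 1,231, Σwt = 1,236 and Σwt² = 7,790.5, so the denominator is 7,790.5 - 1,236²/1,231 = 6,549.5.

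Sustained drop of 3 after diagnosis: Σwd = -3×766 = -2,298 and Σwtd = -3×(1,236+465) = -5,103. The numerator is -5,103 + 1,236×2,298/1,231 = -2,795.7. So γ11 = -2,795.7/6,549.5 = -0.43, γ01 = -1.867 + 0.429 = -1.44, and the fitted 10-year difference is -1.44 - 4.27 = -5.71.

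Drop of 3 recovering linearly by year 10 (d = -3 + 0.3t after diagnosis): Σwd = -2,298 + 0.3×1,701 = -1,787.7 and Σwtd = -5,103 + 0.3×7,325.5 = -2,905.4. The numerator is -2,905.4 + 1,236×1,787.7/1,231 = -1,110.4, so γ11 = -0.17 and γ01 = -1.28.

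The same formula gives the other rows:

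| True RT difference | γ01 | γ11 per year | Fitted at 10 years | True RT effect at 10 years |
|---|---|---|---|---|
| Sustained -3 after diagnosis | -1.44 | -0.43 | -5.71 | -3 |
| -3, recovering linearly by year 10 | -1.28 | -0.17 | -2.98 | 0 |
| -3 in years 0-2 only | -1.24 | 0.00 | -1.23 | 0 |
| Gradual -0.5 per year | -0.26 | -0.43 | -4.55 | -5 |
| Groups differ by -3 beforehand, no RT effect | -3.00 | 0.00 | -3.00 | 0 |

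The sustained drop and the gradual decline give the same γ11. In the recovering case the true postdiagnosis trend is +0.3 per year, so γ11 has the wrong sign. Coding T0 to T10 as 0 to 10 instead gives similar values for the sustained drop (-1.16, -0.42, -5.31).

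**Step 2: allowing for within-woman correlation.** Samples were simulated on the Table 1 layout with 60% RT and SDs of 8 (between) and 6 (within).

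- Sustained 3-point drop, random intercept: mean γ11 from -0.44 to -0.52 per year over repeated runs, significant in 76-87% of samples, fitted 10-year difference about -6.
- The same with a random slope added: -0.57 per year and 73% in one run; 78% significant in another.
- Drop recovering by 10 years: γ11 of -0.21 to -0.24 per year.
- No effect at all: γ11 near 0, significantly negative in 3%.

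A generalized least squares calculation with variances 60 (intercept) and 40 (residual) gives 10-year differences for the sustained drop of -6.1, -7.2 and -8.5 as the random-slope variance goes from 0 to 1 to 4. For the drop confined to years 0-2, γ11 goes from -0.05 to -0.32.

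**Step 3: separate terms.** The Step 1 inputs were refitted with a prediagnosis difference, a postdiagnosis step and a postdiagnosis slope. The results (difference, step, slope) were: sustained drop (0, -3.00, 0.00); prior difference (-3.00, 0, 0); gradual decline (0, 0, -0.50). The drop confined to years 0-2 gives a step of -3.15 and a slope of +0.52, so a straight postdiagnosis line is still too rigid for that case.

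**The case against.** **Equation (1) is a reduced form, and fuller detail may sit elsewhere.** The only stated simplification is that covariates are left out, and adding covariates does not add a step. Curvature is mentioned as a capability, while the printed rule rests on a single γ11.

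**The it subscript could mean that RT switches on after diagnosis.** γ01 would then be a step effect. But the interaction uses subscript i, and the level-2 text puts a yes/no RT variable on the intercept. The notation conflicts with itself and needs settling.

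**γ11 is not always wrong.** This stands. A gradual effect is recovered as -0.38 to -0.43 against -0.50, and a prior group difference leaves γ11 at zero. The printed decision rule concerns γ11 and γ12, so the γ01 problem affects an interpretation, not the stated test.

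**The simulated percentages depend on assumed values.** This also stands. They show that the error can be large, not how large it will be.

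A reader might go further in two ways that the document does not support. One is to call the 10-year difference an extrapolation. There are "92 data points for ≥5 years postdiagnosis", 17 of them at 108 months or later, so it is thinly supported and depends on linearity, and the plan does not promise a projected 10-year figure. The other is to say that γ11 mostly reflects the before-after change because 973 of 1,231 points (79%) fall before 24 months. Slope information is not proportional to counts: in the unweighted fit, points at 5 years or more carry 55% of it and T0 carries 29%.

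**Conclusion.** The concern holds in a conditional form. As printed, the rule on γ11 cannot separate a one-time or temporary drop from a steeper yearly decline, and γ01 cannot be read as what RT adds. Under the stated assumptions, a sustained 3-point drop is reported as a decline of about 0.4 to 0.6 points per year and would be declared significant in roughly three quarters or more of samples. The fitted 10-year difference is then about twice the true one.

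It would go too far to conclude that γ01 and γ11 carry no information on RT. If the effect starts at diagnosis and builds linearly, γ11 is close to right. The plan gives no reason to assume that shape, and its model cannot test it.

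**What to change.** 1. Give RT one consistent subscript in Equation (1) and in the level-2 text.
2. Replace Equation (1) with a model that has a prediagnosis RT group difference, an RT-by-postdiagnosis step and an RT-by-postdiagnosis-time slope. Use spline or categorical time so that a temporary effect can show.
3. Do not force the T0 means to be equal across groups. The groups are not randomised. With no RT effect and a 3-point prior gap, that constraint, or T0 as a covariate with only postdiagnosis scores modelled, gave a false RT effect of about 1 point, significant in 23-33% of 60 simulated samples.
4. Add T0 HRQOL to the propensity model. The Introduction calls baseline HRQOL a major predictor of later HRQOL, but the covariates listed for the weights do not name it.
5. Restate the decision rule in terms of the step and the postdiagnosis slope.
6. Report RT differences with confidence intervals at well-supported times, for example 2 and 5 years. Label later results as sparsely supported and dependent on the assumed time shape. Under Equation (1), with the Step 2 variance assumptions (60 and 40), the standard error of the RT difference is about 0.85-1.0 points at 2 years and 1.8-3.2 at 10 years.

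The cost is plan wording and model code, a somewhat wider interval for the slope, and a shorter horizon for firm conclusions. No new data are needed.
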